#### 7.1.2.3 BLOOD SAMPLING

At visits specified in the Schedule of Events, blood samples will be collected for lot-to-lot consistency and immune non-inferiority assessments of OCV-S compared to Shanchol™.

#### 7.1.2.4 TOTAL DURATION

This study will last approximately 6.5 months. This duration period will be taken from the first dose vaccination to the last safety follow up. All the participants receiving OCV-S and Shanchol™ will be follow up for 6 months after the last dose until the end of the study.

---

### 7.1.3 VISIT PROCEDURES

Details of visit procedures during screening are as follows and summarized information is found in [Table 2. Study Procedures/Schedule of Events](#).

#### **Visit 1. Screening (Days -7 to 0)**

- 1) Explain study objectives and procedures, risk and benefits to the participant /parent(s) /LAR.
- 2) Obtain written informed consent/assent from the participant/parent(s)/LAR. Written Informed consent/assent forms will be obtained prior to performing any study-specific screening or evaluations.
- 3) Obtain medical/medication history of last 1 year, demographics including date of birth, gender and perform physical examination including vital signs and height/weight and record in study database.
- 4) Perform screening procedures within 0 to 7 days prior to first vaccination
- 5) Check if participants meet inclusion/exclusion criteria.
- 6) Determine if participants are qualified to participate in this study and confirm by documenting on the medical record and into the study database. For participants who are not eligible, the reason(s) must be recorded.

- 7) All married female participants of childbearing age will be screened with urinary pregnancy test and whether using any contraceptive method or not. If un-married female participants of childbearing age agree to take pregnancy test, the test should be performed.
- 8) Pregnancy Prevention Counseling: Clinical staff should perform pregnancy prevention counseling on female participants of childbearing potential to evaluate if participants are able to meet the birth control eligibility criteria.
- 9) Schedule participants for vaccination visit (Visit 2) at the study center within 7 days after the screening visit. If an eligible participant does not come back for vaccination within the 7 days after the screening visit, screening procedures must be repeated.
- 10) Screening and enrollment visit could be performed on the same day if the screening related information can be obtained on the date of screening.
- 11) Participant who does not meet the criteria for participation in this trial because of fever or acute illness, may be rescreened when these conditions have resolved. Rescreened participants will be assigned the same screening number as for the initial screening.

## **Visit 2. Enrollment / 1st dose Vaccination / Blood drawing (Day 0)**

- 1) Obtain medical/medication history of last 1 year and perform physical examination including vital signs and record in eCRF.
- 2) Perform urinary pregnancy test for all married female participants of childbearing age. If un-married female participants of childbearing age agree to take pregnancy test, the test should be performed.
- 3) Confirm eligibility of participant for the first dose of vaccination.
- 4) Perform enrollment, randomization and attribute enrollment number to participant.
- 5) Collect a venous blood sample prior to immunization; See Table below.

**Table 5. Blood Sample Volume by Age**

| Age of participants | 1-5 Years          | 6-40 Years         |
|---------------------|--------------------|--------------------|
| Blood sample volume | Approximately 4 mL | Approximately 6 mL |

\*Minimum volume for 1-5 years old is 3 mL.

- 6) Vaccinate the first dose vaccine.
- 7) Monitor participant for 30 minutes following vaccination as follows:
  - Clinical examination including vital signs, general physical examination before leaving the study center 30 minutes post vaccination

- Record adverse reactions (if any occurrence is there)
- 8) Instruct participant/parent(s)/LAR to record any adverse event at home for 7 days post immunization (from Day 0 to Day 6) in diary card (DC) 1.
  - 9) If Day 7 visit will be through phone call, provide DC2 to record unsolicited adverse events (if any occurrence is there) during Day 7 to Day 13 and instruct participant/parent(s)/LAR how to fill in the diary card.
  - 10) Provide a thermometer along with DC1 to record fever.
  - 11) Schedule next home visit/phone call (HV/PC) at Day 7 and next visit to the study site at Day 14 and remind participant(s)/parent/LAR to bring the DC1 and DC2 (for PC1), if distributed, at the next visit. If HV/PC may not be applicable depending on situation (e.g., COVID-19 situation), it may be replaced by a site visit.
  - 12) Instruct participant/parent(s)/LAR to contact investigator/study staff if needed.

#### **Home visit/Phone call 1. Post 1st dose 1-week safety follow-up (Day 7 / Week 1 $\pm$ 1 days)**

Each participant will be followed up for safety via home visit at Day 7 after the first dose of vaccination. A visiting site staff will,

- 1) Verify and collect recorded DC1 and confirm with participant/parent(s)/LAR.
- 2) Record solicited and unsolicited events and concomitant medications in DC1 in study database.
- 3) Provide DC2 to document any unsolicited adverse events (if any occurrence is there) during Day 7 to Day 13 before the next visit
- 4) Remind to bring DC2 at Visit 3 on Day 14.
- 5) Remind to visit the site for the second dose of vaccination at Day 14.
- 6) Remind the participant/parent(s)/LAR to contact investigator/ study staff if needed.

Home visit may be replaced by a phone call. Only a qualified healthcare professional (HCP) according to Nepal's definition of HCP (*i.e.*, registered physician, health assistant nurse practitioner, public health nurse, auxiliary health worker), should perform the call. A staff calling the participants will,

- 1) Check the participant's identification.
- 2) Call out all the solicited adverse events listed in DC1 to participant(s)/parent/LAR so that the adverse events can be confirmed through the call.

- 3) Enter the adverse events in DC1 into eCRF when DC1 is collected.
- 4) Instruct to document any adverse events (if any occurrence is there) during Day 7 to Day 13 in DC2 and remind to bring DC1 and DC2 at Visit 3 on Day 14.

Home visit/phone call maybe replaced by a site visit.

Each AE will be assessed according to the following method:

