**Visit 3. 2nd dose Vaccination / Blood drawing (Day 14 / Week 2 + 3 days)**

- 1) Obtain medical/medication history and perform physical examination including vital signs and record in the eCRF.
- 2) Verify and record all unsolicited AEs and concomitant medications in DC2 and record in the eCRF.
- 3) Perform urinary pregnancy test for all married female participants of childbearing age. If unmarried female participants of childbearing age agree to take pregnancy test, the test should be performed.
- 4) Confirm eligibility of participant for the second dose vaccination.
- 5) Collect a venous blood sample prior to immunization; See Table below.

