**Visit 4. Post 1st dose 4-week Safety follow up / Blood drawing (Day 28 / Week 4 ± 3 days)**

Each participant will be followed up for safety and blood drawing.

- 1) Verify and collect DC4 and confirm with participant/parent(s)/LAR enter any unsolicited events and concomitant medications CRF
- 2) Provide DC5 to document unsolicited adverse events (if any occurrence is there) from Day 28 to Day 41. Instruct participant/parent(s)/LAR how to fill in the diary card.
- 3) If Day 42 visit will be through phone call, provide DC6 to record adverse events (if any occurrence is there) during Day 42 to Day 181.
- 4) Schedule next HV/PC3 at Day 42 and next visit to the study site at Day 182 and remind participant(s)/parent/LAR to bring the DC5 and DC6, if distributed, at the next visit. If HV/PC may not be applicable depending on situation (e.g., COVID-19 situation), it may be replaced by a site visit.
- 5) Instruct participant/parent(s)/LAR to contact investigator/study staff if needed.
- 6) Collect a venous blood sample prior to immunization; See Table below.

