### 10.3 TIME PERIOD AND FREQUENCY FOR EVENT ASSESSMENT AND FOLLOW-UP

All participants will be observed for immediate adverse reactions for 30 minutes after each vaccination. For 7 consecutive days (Days 0-6) after each dose of study vaccine, the participant/parent(s)/LAR will be asked to record solicited symptoms in the diary card. The study staff will remind participant/parent(s)/LAR of the importance of properly filling the diary cards and to return the cards at the next scheduled study visit. If they did not fill up or lost their card, the

participant/parent(s)/LAR will be interviewed for recall of symptoms with trained study staff during clinic visit on Day 7 after vaccination.

The occurrence of an adverse event (AE) will come to the attention of study personnel during study visits and interviews of a study participant presenting for medical care, or upon review by a study monitor.

All AEs not meeting the criteria for SAEs will be captured on the appropriate case report form (eCRF). Information to be collected includes event description, time of onset, symptoms and physical examination findings, clinician's assessment of severity, relationship to study product (as assessed by the PI or delegated SI), medications given and time of resolution/stabilization of the event. All AEs occurring while on study will be documented appropriately regardless of relationship.

Changes in the severity of an AE will be documented to allow an assessment of the duration of the event at each level of severity to be performed. AEs characterized as intermittent require documentation of onset and duration of each episode.

The investigator will record all reportable events with start dates occurring any time after informed consent is obtained until the last day of study participation. At each study visit, the investigator will inquire about the occurrence of AE/SAEs since the last visit. Events will be followed for outcome information until resolution or stabilization.

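### The visit windows allow diary cards to be collected before their last covered day is over, so a few end-of-window adverse events may be missed or rest on recall

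*Protocol*

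**What the plan says.** Section 10.3 has solicited symptoms recorded "For 7 consecutive days (Days 0-6) after each dose of study vaccine". At Visit 2, participants are told to "record any adverse event at home for 7 days post immunization (from Day 0 to Day 6") on DC1. The first home contact, headed "1-week safety follow-up (Day 7 / Week 1 $\pm$ 1 days"), has a window of one day either side, and its first step is "Verify and collect recorded DC1 and confirm with participant/parent(s)/LAR." Its third step is "Provide DC2 to document any unsolicited adverse events (if any occurrence is there) during Day 7 to Day 13 before the next visit".

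The later cards follow the same pattern:

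- **DC3** covers Days 14-20 and is collected at the Day 21 contact (± 1 day).
- **DC4** covers Days 21-27 and is collected at Visit 4 (Day 28 ± 3 days), where staff "Provide DC5 to document unsolicited adverse events (if any occurrence is there) from Day 28 to Day 41".
- **DC5** is collected at the Day 42 contact (± 1 day), and DC6 runs from Day 42 to Day 181.

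DC2 is the exception, because Visit 3 has no minus side: "Blood drawing (Day 14 / Week 2 + 3 days").

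Table 2 marks solicited events only at Days 7 and 21. Table 7 runs the unsolicited windows over Days 0-28 and Days 14-42. Section 13.1.2 makes solicited events within 7 days and unsolicited events within 28 days part of the primary safety endpoint.

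**The concern.** The card dates and the visit windows do not fit together. A site can stay fully within window and still take a card back before its last day has ended, while the next card is labelled to start later. On the home-visit route DC2 is also given a narrower job than DC1, since it takes unsolicited events only.

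A participant seen early therefore contributes fewer diary days than the endpoint states but counts fully in the denominator. How often this happens depends on each site's scheduling. What is at stake is the completeness of the absolute adverse event frequencies.

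**Working it through.** The check is a day count for a participant dosed on schedule. Earliest collection day = nominal day minus the window; this is compared with the card's last day and the first day of the next card. The stated solicited window reproduces: Days 0-6 and Days 14-20 are 7 days each.

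| Card | Covers | Collected at | Earliest day | Next card from | On no card |
|---|---|---|---|---|---|
| DC1 | 0-6 | Day 7 ± 1 | 7 − 1 = 6 | 7 | rest of Day 6 |
| DC2 | 7-13 | Day 14 + 3 | 14 | 14 | nothing |
| DC3 | 14-20 | Day 21 ± 1 | 21 − 1 = 20 | 21 | rest of Day 20 |
| DC4 | 21-27 | Day 28 ± 3 | 28 − 3 = 25 | 28 | rest of Day 25, Days 26-27 |
| DC5 | 28-41 | Day 42 ± 1 | 42 − 1 = 41 | 42 | rest of Day 41 |

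With every visit on its nominal day there is no gap.

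**Solicited exposure.** Less than 1 of 7 days per dose, so under 1/7 = 14.3%, and only for participants whose card is collected on Day 6 or Day 20. If a share f of participants is seen that early, at most f × 14.3% of solicited person-days are lost. The protocol gives no f. An assumed one third gives at most 4.8%, and the full range is 0 to 14.3%.

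For scale, Table S4 reports solicited events after dose 1 in 3.96% of Group C and 2.78% of Group D. Suppose everyone was seen on Day 6, the whole day was lost, onsets were uniform and nothing was recalled. The complete figures would then be roughly 3.96 / (6/7) = 4.62% and 2.78 / (6/7) = 3.24%. With half a day lost they would be 3.96 / (6.5/7) = 4.26% and 2.78 / (6.5/7) = 2.99%. These are upper-end illustrations, not estimates.

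**Unsolicited exposure at Visit 4.** More than 2 and less than 3 days, that is 2/28 = 7.1% to 3/28 = 10.7% of a 28-day window, for a participant seen on Day 25. These days lie in both Table 7 windows.

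**What could catch these events later:**

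- *Late Day 6 or Day 20.* Visit 3 step 2 reviews unsolicited events in DC2, and no visit after Day 21 is marked for solicited events. The recall interview in section 10.3 is for cards not filled in or lost. What remains is the general inquiry at each study visit, which for Day 6 comes 14 − 6 = 8 days later at the nominal Visit 3.
- *Days 25-27.* The Day 42 home visit records unsolicited events since the last visit, a recall of 42 − 27 = 15 to 42 − 25 = 17 days. The phone script for the same contact reads out only events listed in DC5, whose label starts at Day 28.
- *Late Day 41 and Day 42.* Day 42 is on DC6. Visit 5 step 2 records DC5 and DC6 in the study database, but step 3 limits the eCRF to SAEs and concomitant medication. A non-serious event on Day 42 therefore has no clear route into the eCRF, although Table 7 includes that day.

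**The case against.** The strongest reply is that the cards are not the only source. Tables 6 and 7 list observation and interview beside the diary card. Section 10.3 requires an inquiry about adverse events at each study visit, and the Day 42 home visit asks about unsolicited events since the last visit. On the phone route, DC1 to DC4 stay with the participant until Visit 3 or Visit 4. Contacts are to be scheduled on the nominal day, and the window is only a tolerance.

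Much of this stands. It confines the DC1 and DC3 gaps to home or site visits made early, and it means unsolicited events in the Visit 4 gap can still be recorded. It does not close the solicited gap, because no later contact solicits those symptoms. The phone route does not help at Visit 4 either, since DC4 is handed in there in any case. Home visit is also the default contact in section 7.1.3, with the phone call as a replacement.

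A reader might infer three stronger things that the document does not support:

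- *That the frequencies are understated.* This would require knowing how many contacts fell early and what recall missed; neither is given.
- *That Day 42 is on no card.* It is on DC6; the difficulty there is eCRF entry.
- *That one vaccine is favoured.* The windows are the same in all groups and assessors are blinded.

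A fair warning also applies to the remedy. Starting each new card on the collection day, without extending the old one, would open gaps after late visits. With Visit 4 on Day 31, for example, Days 28-30 would be on neither DC4 nor DC5.

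**Conclusion.** The mismatch is real and follows from the protocol's own dates. The primary safety frequencies may be slightly incomplete, or may rest on recall in place of a daily card. For a participant seen on the earliest permitted day, the exposure is under 1 of 7 solicited days after each dose (home or site visits only) and under 3 of about 28 unsolicited days at Visit 4.

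The overall effect cannot be sized, because the share of early contacts is unknown, and it is small if onsets cluster soon after the dose. The percentages assume on-schedule dosing, and reading them as lost events also assumes uniform onset and no recall. No bias between vaccines is expected. This is a cheap improvement to data capture, not a threat to the trial's conclusions.

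**What to change.** 1. Make the Day 7, 21 and 42 card-collecting contacts one-sided, no earlier than the nominal day; 0 to +2 days would keep the present three-day width.
2. State that each card stays open until it is actually collected and that the next card starts that day. Assign events to the 7-day or 28-day window by onset date. Neither early nor late visits then leave a gap, including a Visit 3 on Day 17, where DC2 now ends on Day 13 and DC3 is not handed out until Day 17.
3. If Visit 4 falls before Day 28, start DC5 on the actual Visit 4 date. The blood-sampling window is unchanged.
4. Reconcile Visit 5 steps 2 and 3 with the Days 14-42 window, so that non-serious events with onset in that window reach the eCRF.

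The cost is wording in Table 2, section 7.1.3 and the diary-card instructions, with no extra visits or participants. The downside is slightly less scheduling freedom and up to one extra day of recall, since the latest first contact would move from Day 8 to Day 9.

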**Table 6. Assessment method of Solicited General Adverse Events**

| Assessment method                                                           |                                          |
|------------------------------------------------------------------------------------|------------------------------------------|
| Solicited General Adverse Events (Days 0-6 and Days 14-20)                  |                                          |
| Nausea/Vomiting, Diarrhea, Headache, Fatigue, Myalgia, Anorexia (loss of appetite) | General observation/interview/diary card |
| Fever                                                                              | Thermometer/interview/diary card         |

**Visit 3. 2nd dose Vaccination / Blood drawing (Day 14 / Week 2 + 3 days)**

- 1) Obtain medical/medication history and perform physical examination including vital signs and record in the eCRF.
- 2) Verify and record all unsolicited AEs and concomitant medications in DC2 and record in the eCRF.
- 3) Perform urinary pregnancy test for all married female participants of childbearing age. If unmarried female participants of childbearing age agree to take pregnancy test, the test should be performed.
- 4) Confirm eligibility of participant for the second dose vaccination.
- 5) Collect a venous blood sample prior to immunization; See Table below.

**Table 5. Blood Sample Volume by Age**

| Age of participants | 1-5 Years          | 6-40 Years         |
|---------------------|--------------------|--------------------|
| Blood sample volume | Approximately 4 mL | Approximately 6 mL |

\*Minimum volume for 1-5 years old is 3 mL.

- 6) Vaccinate the second dose vaccine.

- 7) Monitor participant for 30 minutes following vaccination as follows:
  - Clinical examination including vital signs, general physical examination before leaving the study center 30 minutes post vaccination.
  - Record adverse reactions (if any occurrence is there)
- 8) Instruct participant/parent(s)/LAR to record any adverse event at home for 7 days post immunization (from Day 14 to Day 20) in DC3.
- 9) If Day 21 visit will be through phone call, provide DC4 to record adverse events (if any occurrence is there) during Day 21 to Day 27 and instruct participant/parent(s)/LAR how to fill in the diary card.
- 10) Schedule next HV/PC2 at Day 21 and next visit to the study site at Day 28 and remind participant(s)/parent/LAR to bring the DC3 and DC4 , if distributed, at the next visit. If HV/PC may not be applicable depending on situation (e.g., COVID-19 situation), it may be replaced by a site visit.
- 11) Instruct participant/parent(s)/LAR to contact investigator/study staff if needed.

**Home visit/Phone call 2. Post 2nd dose 1-week Safety follow-up (Day 21 / Week 3  $\pm$  1 days)**

Each participant will be followed up for safety via home visit at Day 21. A visiting site staff will,

- 1) Verify and collect recorded DC3 and confirm with participant/parent(s)/LAR.
- 2) Record solicited, unsolicited AEs and concomitant medications since last visit in eCRF.
- 3) Provide DC4 to document any unsolicited AE (if any occurrence is there) during Day 21 to Day 27 before the next visit.
- 4) Remind to bring DC4 at the next visit.
- 5) Remind to visit the site at Day 28.
- 6) Remind to contact investigator/ study staff if needed.

Home visit may be replaced by a phone call. Only a qualified healthcare professional (HCP) according to Nepal's definition of HCP (*i.e.*, registered physician, health assistant nurse practitioner, public health nurse, auxiliary health worker), should perform the call. A staff calling the participants will,

- 1) Check the participant's identification.
- 2) Call out all the solicited and unsolicited AEs listed in DC3 to participant(s)/parent/LAR so that the AEs can be confirmed through the call.

- 3) Enter the solicited, unsolicited AEs and concomitant medications into the study database when DC3 is collected.
- 4) Instruct participant(s)/parent/LAR to document any adverse events (if any occurrence is there) during Day 21 to Day 27 in DC4, provided on Day 14, and remind to bring DC3 and DC4 at Visit 4, Day 28.

Home visit/phone call maybe replaced by a site visit.

Each AE will be assessed according to the following method:

**Table 6. Assessment method of Solicited General Adverse Events**

| Assessment method                                                           |                                          |
|------------------------------------------------------------------------------------|------------------------------------------|
| Solicited General Adverse Events (Days 0-6 and Days 14-20)                  |                                          |
| Nausea/Vomiting, Diarrhea, Headache, Fatigue, Myalgia, Anorexia (loss of appetite) | General observation/interview/diary card |
| Fever                                                                              | Thermometer/interview/diary card         |

**Visit 4. Post 1st dose 4-week Safety follow up / Blood drawing (Day 28 / Week 4 ± 3 days)**

Each participant will be followed up for safety and blood drawing.

- 1) Verify and collect DC4 and confirm with participant/parent(s)/LAR enter any unsolicited events and concomitant medications CRF
- 2) Provide DC5 to document unsolicited adverse events (if any occurrence is there) from Day 28 to Day 41. Instruct participant/parent(s)/LAR how to fill in the diary card.
- 3) If Day 42 visit will be through phone call, provide DC6 to record adverse events (if any occurrence is there) during Day 42 to Day 181.
- 4) Schedule next HV/PC3 at Day 42 and next visit to the study site at Day 182 and remind participant(s)/parent/LAR to bring the DC5 and DC6, if distributed, at the next visit. If HV/PC may not be applicable depending on situation (e.g., COVID-19 situation), it may be replaced by a site visit.
- 5) Instruct participant/parent(s)/LAR to contact investigator/study staff if needed.
- 6) Collect a venous blood sample prior to immunization; See Table below.

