| Diary Card (DC) Distribution            |                                                        | DC1 | DC2            | DC3     | DC4              | DC5               | DC6                |                      |                   |
| Diary Card (DC) Collection              |                                                        |     | DC1            | DC2**** | DC3              | DC4****           | DC5                | DC6                  |                   |
| Solicited Adverse Events                |                                                        |     | X              |         | X                |                   |                    |                      |                   |
| Unsolicited Adverse Events              |                                                        | X   | X              | X       | X                | X                 | X                  |                      | X                 |
| Study Completion Form                   |                                                        |     |                |         |                  |                   |                    | X                    |                   |
| SAE/Pregnancy Reporting                 | To be reported at any time throughout the study period |     |                |         |                  |                   |                    |                      |                   |

† 7 days post 1st dose vaccination

†† 7 days post 2nd dose vaccination

††† 28 days post 1st dose vaccination

†††† 28 days post 2nd dose vaccination

††††† 6 months post 2nd dose vaccination

\* Home visits/Phone calls

\*\* Pregnancy Test is necessary for all married female participants of childbearing age. If un-married female participants of childbearing age agree to take pregnancy test, the test should be performed.

\*\*\* After D42, concomitant medication history related to SAEs only will be recorded

\*\*\*\* For safety follow ups through phone calls, DC1,2 and DC 3,4 will be collected on V3 and V4, respectively.

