#### **Visit 5. Post 2nd dose 24 week/6 months Safety follow up (Day 182 / Week 26 ± 5 days)**

Each participant will be followed up for safety.

- 1) Verify and collect recorded DC5 and DC6 and confirm with participant/parent(s)/LAR.
- 2) Record DC5 and DC6 in study database.
- 3) Only SAE and concomitant medication will be collected in the eCRF.
- 4) Instructed to contact investigator/study staff if needed.
- 5) Ensure source documents are completed before the participant/parent/LAR leave the study site.
- 6) For unresolved AEs, participants will be continued to be monitored after study ends.

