#### 7.2.15 PROTOCOL DEVIATIONS

The ICH E3 Q&A R1 defines a protocol deviation (PD) as “any change, divergence, or departure from the study design or procedures defined in the protocol.” In other words, protocol deviation is any noncompliance with the clinical trial protocol, ICH E6 (R2) GCP, E11 (R1) or MOP requirements by the participant, the investigator, or the study site staff. It is the responsibility of the site PI to use continuous vigilance to identify and report all protocol deviations to the site IRB/IEC and to the sponsor. The PI is responsible for knowing and adhering to the site requirements. The IVI Study Medical Monitor will report all protocol deviations to IVI IRB/IEC and only major PDs have to be reported to IVI IRB/IEC within 10 calendar days of their awareness.

The ICH guidelines also introduce a definition for “important” protocol deviations, defining them as “a subset of protocol deviations that may significantly impact the completeness, accuracy,

and/or reliability of the study data or that may significantly affect a participant's rights, safety, or well-being." Important, "major", "critical" and "significant" are synonyms when referring to important protocol deviations.

To align the sponsor terminology with that of the health authorities' (*i.e.*, Regulatory Agency inspectors), we are using the terminology major and minor instead of the classification of important and non-important protocol deviations.

Major deviations are defined as those jeopardize the safety or rights of the participant or the scientific integrity of the study which is applicable to cases listed below.

- Violation of inclusion and exclusion criteria
- Vaccination with wrong vaccine as defined in the protocol
- Vaccination outside window of the immunization schedule defined in protocol
- Missed visit or visit outside window for the immunogenicity assessment

Major protocol deviations thought to affect the scientific integrity of the study and/or the safety and rights of the participant will be reported and discussed with investigator, monitor, sponsor, and statistician for their exclusion from the per protocol analysis.

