## 13. STATISTICAL CONSIDERATIONS

### 13.1 STUDY ENDPOINTS

#### 13.1.1 PRIMARY IMMUNOGENICITY ENDPOINT

- Proportion of participants showing seroconversion of vibriocidal titers against *Vibrio cholerae* O1 Inaba and O1 Ogawa (seroconversion is defined as at least 4-fold increase of vibriocidal titers against *V. cholerae* O1 Inaba and O1 Ogawa compared to baseline) at 2 weeks after second dose of either OCV-S (*i.e.*, one lot of OCV-S) or Shanchol™ for all ages.

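### The primary-endpoint blood draw is scheduled from dose 1 (Day 28 ± 3), so a compliant sample for the endpoint 2 weeks after dose 2 can be taken 8 to 17 days after dose 2

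*Protocol*

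**What the plan says.** All references are to the protocol.

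- **Endpoint.** Section 13.1.1 defines the primary immunogenicity endpoint as seroconversion "at 2 weeks after second dose of either OCV-S" or Shanchol. Sections 13.4 and 13.6.3 use the same time point, as do the GMT and lot-consistency endpoints in 13.1.3.
- **Dose 2.** Visit 3 in Section 7.1.3 is headed "Blood drawing (Day 14 / Week 2 + 3 days", so dose 2 may be given on Day 14, 15, 16 or 17. Table 2 agrees.
- **Endpoint sample.** Visit 4 is headed as a post-first-dose visit: "dose 4-week Safety follow up / Blood drawing (Day 28 / Week 4 ± 3 days". The Table 2 footnote for it reads "28 days post 1 st dose vaccination". The footnotes for the Day 21, Day 42 and Day 182 contacts refer to dose 2, so Visit 4 is the only contact after dose 2 that is tied to dose 1.
- **Per-protocol rule.** Section 7.2.15 lists as a major deviation "Missed visit or visit outside window for the immunogenicity assessment". Major deviations are discussed for exclusion from the per-protocol set (PPS), and Section 13.5 makes the PPS the primary set for immunogenicity.
- **Safety diaries.** Visit 3 gives DC3 the dates Day 14 to Day 20. Visit 4 gives DC5 to "document unsolicited adverse events (if any occurrence is there) from Day 28 to Day 41". At Visit 5, "Only SAE and concomitant medication will be collected in the eCRF". Section 10.4.1 has adverse events collected to the end of the trial, in both source documents and eCRF.

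**The concern.** The endpoint is counted from dose 2, and the visit that measures it is counted from dose 1. The two agree only if dose 2 is given on Day 14, or if any delay in dose 2 is matched by an equal delay in the draw. Nothing in the protocol asks for that match, and no section gives a draw window counted from the actual date of dose 2.

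Two things are at stake. First, samples well short of 2 weeks after dose 2 count as compliant measurements of the endpoint. Second, the timing criterion for the primary analysis set ranks samples on the wrong scale: it accepts some that are further from 14 days than others it flags. The same sample serves the primary comparison, the secondary non-inferiority comparisons and lot consistency.

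**Working it through.** **Plan's own figures.** The nominal interval is 28 − 14 = 14 days, which matches the endpoint. The stated power also reproduces. With rate p = 0.71 in both arms, margin 0.10 and one-sided alpha 0.025, power = Φ(0.10 / √(2p(1 − p)/n) − 1.96).

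- n = 935: standard error 0.0210, power 0.9975.
- n = 841 (935 less 10% dropout): standard error 0.0221, power 0.9948.

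Both agree with the stated 99%.

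**Interval from dose 2 to the sample.** Inputs are dose 2 on Day 14 to 17 (Visit 3) and the draw on Day 25 to 31 (Visit 4). Interval = draw day − dose-2 day.

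| Dose 2 on | Earliest in-window draw | Latest in-window draw | 14-day draw falls on |
|---|---|---|---|
| Day 14 | 25 − 14 = 11 days | 31 − 14 = 17 days | Day 28 |
| Day 15 | 10 days | 16 days | Day 29 |
| Day 16 | 9 days | 15 days | Day 30 |
| Day 17 | 8 days | 14 days | Day 31 |

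The overall range is 8 to 17 days. The last column shows that a draw at exactly 14 days is always in window. After a Day 17 dose, however, the window runs from 6 days early to 0 days late around the 14-day target.

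**Comparison with a window counted from dose 2.** Take 14 ± 3 days from dose 2, i.e. 11 to 17 days. The ± 3 is borrowed from Visit 4; the protocol states no window on this scale. There are 4 × 7 = 28 permitted day pairs (dose 2/draw).

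- Counted as compliant at only 8 to 10 days: 15/25, 16/25, 16/26, 17/25, 17/26, 17/27 (6 of the 28).
- Flagged as out of window although at 15 to 17 days: 15/32, 16/32, 16/33, 17/32, 17/33, 17/34 (6 further pairs).

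For a Day 17 dose, a Day 25 draw (8 days, 6 off target) is compliant and a Day 32 draw (15 days, 1 off target) is a major deviation. After a Day 14 dose, a draw at 17 days (Day 31) is compliant. These are counts of possible day pairs, not of participants; the protocol does not say how many receive dose 2 after Day 14.

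**Post-dose-2 safety dates, if read as calendar days.**

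- DC3, Days 14 to 20: a Day 17 dose leaves Days 17 to 20, four of the seven days.
- Day 21 ± 1 contact: as early as 20 − 17 = 3 days after dose 2.
- Day 42 ± 1 contact: as early as 41 − 17 = 24 days after dose 2.
- DC5 ends on Day 41; 28 days after a Day 17 dose is Day 45.

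The Table 2 footnotes (7 and 28 days after dose 2), Section 10.3 (seven consecutive days after each dose) and the endpoint in 13.1.2 point to dose 2 instead. Calendar dates and dose-2 anchors cannot both hold for a dose given on Day 15 to 17.

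**The case against.** The best defence has four parts.

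- **Exclusion is not automatic.** Section 7.2.15 sends major deviations to discussion, and Section 13.5 rests the PPS on important deviations as assessed by the medical monitor. This stands: the rule marks samples for possible exclusion. No draw at exactly 14 days is marked.
- **Few samples may be affected, and the full analysis set is analysed too.** In the result tables appended to the protocol, the adult OCV-S groups number 327 + 322 + 323 = 972 in the full analysis set and 308 + 311 + 312 = 931 in the per-protocol lot-consistency table. The gap for all reasons is 41 (4.2%). This limits how many draws could have been wrongly excluded in those groups. It says nothing about how many early draws were kept.
- **The day window belongs in the SAP.** A SAP could define the PPS window from dose 2. It cannot turn a sample taken 8 days after dose 2 into one taken at 14, and the protocol itself fixes the visit and the deviation rule.
- **Safety contacts are anchored to dose 2.** By footnote and heading they are. What remains is a conflict between those anchors and the fixed dates, and between Visit 5 and Section 10.4.1. DC6 continues to collect any adverse event after Day 42, so lost safety data are not established.

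A reader might also infer that timing noise common to both arms favours non-inferiority. The same window applies to both arms under randomisation and observer blinding, and nothing in the protocol shows a shift in the difference. Nor does the fall in adult seroconversion between the two post-dose samples in Table S3 give a rate of change over days 8 to 17 after dose 2. A vaccination lies between those samples. The fall also differs by serotype (Ogawa 2.9 to 6.2 points, Inaba 1.0 to 4.5), and a change over time is not a between-arm difference to set against the 10-point margin.

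**Conclusion.** The point holds as a mismatch between the endpoint definition and the visit that measures it, and should be fixed. Compliant samples fall 8 to 17 days after dose 2 against a 14-day definition. The deviation rule for the primary analysis set accepts draws at 8 to 10 days and flags draws at 15 to 17 days after a late dose 2. The 8-to-17-day range follows directly from the two stated windows. The six-and-six count rests on the assumed 14 ± 3 day comparison window.

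No direction of bias is shown. The stated power does not depend on this point: at 841 per arm, the formula above gives 0.984 to 0.999 for common seroconversion rates from 50% to 80%. The cost is a blurred time point and a per-protocol criterion that does not match the endpoint. On safety, the finding is limited to inconsistent dates and recording instructions that need reconciling.

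**What to change.** 1. In Table 2 and Section 7.1.3, schedule the Visit 4 blood draw at the actual dose-2 date + 14 days, with the ± 3 day window on that scale (11 to 17 days). Correct the Visit 4 heading and footnote to match. The permitted draw then spans Day 25 to Day 34.
2. In Section 7.2.15, define the immunogenicity-window deviation for the post-dose-2 sample as days since dose 2, and use the same definition for the PPS in 13.5.
3. Reconcile the fixed post-dose-2 dates (DC3 Days 14 to 20, the Day 21 contact, DC5 to Day 41, the Day 42 contact, Tables 6 and 7) with the footnotes that count from dose 2 and with the 7-day and 28-day safety endpoints. Visit 4 also serves the dose-1 28-day follow-up and is where DC4 is collected, so the DC4 and DC5 dates must meet on the new visit date.
4. Reconcile Visit 5 with Section 10.4.1 on which events after Day 42 enter the eCRF.

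The dose-2 window itself need not change. The cost is protocol wording and visit-date logic in the trial systems, with no extra visits, samples or participants. If samples have already been drawn, tabulate days from dose 2 to the draw by arm and define the PPS window on that scale before unblinding; this cannot recover draws already taken early.
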